The core of the interviews consists of hypothetical clinical and research vignettes specifically designed to elicit older adult preferences and assess the ability of their proxy to predict these preferences. Vignettes are modeled on those developed and validated by us and others [7-9,43-45] in previous research on substitute decision-making. Responses are elicited under four health states: 1) the subject's current health state, 2) as if he/she had sustained a light to moderate stroke, 3) as if he/she had an incurable brain cancer, and 4) as if he/she had severe dementia. The concordance assessment begins by asking older adults to imagine themselves in each of these states and select the answers that best describe their quality of life under these states (from excellent to poor). Then, for each health state, they are asked to indicate whether they would want to receive each of five life-sustaining treatments (antibiotics, CPR, etc.). The same exercise is repeated at the second interview, this time seeking the older adults' willingness to enroll in each of three research protocols (blood sample, supervised exercise program, and oral medication trial). These protocols are designed to cover a broad range of risks and benefits (to the subject or others) in order to elicit an equally broad spectrum of willingness to participate. Older adults are also asked to select one out of four goals of care (from palliative care to intensive care) for different sudden health events (pneumonia, hemorrhagic shock, and severe head trauma). Health events were chosen to capture a wide range of conditions varying in severity, nature of impairment, and prognosis. To ensure understanding, health states, treatment modalities, research protocols and critical events are described briefly and simply by the research nurse using written materials handed out during training. Using identical response scales, proxies are asked to choose the decision they think the older adult will make in each situation (substituted judgment) or, if unable to do so, to make a decision based on the older adult's best interests. Concordance assessments were pre-tested on three potential dyads and subsequently revised for clarity. Results are compiled as soon as the interviews are completed, and communicated to experimental dyads at the start of the intervention.

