### Trial interventions

#### Intervention in the experimental group

The proposed intervention was designed from literature reviews [6,39,40] and recent experimentations [31,33]. It integrates multiple methods to increase learning [46] and uses teaching tools adapted to normal aging changes [47]. The intervention consists of 2-hour meetings, once monthly, over three months. The duration of the intervention follows from the need for an incremental process that enables older adults to articulate preferences at their own pace and gradually integrate information on the benefits and limitations of ADs [28]. Furthermore, we expect repeated encounters to foster trusting relationships between dyad members and research personnel that are conducive to discussions on issues as sensitive as end-of-life care. The first and third meetings take place in the home of the older adult or proxy, a strategy likely to counter attrition [31]. The second meeting is an information session on ADs for groups of dyads.

Home meetings are led by trained social workers with extensive experience working with elders. The first visit begins with two thought-provoking vignettes that highlight the importance of communicating one's wishes about future medical care and research participation. The use of vignettes illustrating real-life experience has been shown to increase learning in elderly populations [47]. After eliciting reactions to the vignettes and exploring related issues, the facilitator summarizes the dyad-specific results of the concordance assessment and invites dyad members to discuss the reasons underlying their choices. Discussions seek to help older adults describe what makes their life worth living in specific, functional terms [48] and articulate their wishes, personal values and beliefs, so as to guide proxies in making decisions for them. Throughout the intervention, the social worker catalyzes discussion so that a shared understanding gradually develops between the older adult and his/her proxy.

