#### Intervention in the control group

Approximately once monthly over three months, dyads assigned to the control group are invited to attend a 2-hour health education workshop on healthy lifestyle and preventive practices. The three workshops are adapted from a health education program aimed at improving self-care skills that has been effective with elderly people [66]. The number of meetings between dyads and the research team is identical across groups. However, experimental dyads meet individually and in subgroups whereas controls always convene in subgroups. Health education workshops are given by experienced nurses and allow for interaction within and between dyads. Once the study is complete, the AD information session given to experimental dyads will be offered to controls.

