### Primary and secondary outcome measures

Prediction accuracy of substitute decision-making is the primary outcome and rate of completed guides, the secondary outcome. Concordance is the most important outcome of advance planning activities. However, we consider important to also measure the rate of documented preferences as these could raise less controversy in the event of incompetence than oral instructions given only to a single family member.

Concordance assessments are repeated at the end of the intervention (first posttest) and 6 months later (second posttest), according to the same procedure as at baseline. However, the first posttest uses new sets of treatments, sudden health events and research protocols to counter recall bias. Older adults' decisions under these various scenarios, and their proxies' predictions concerning those decisions, are recorded by the same research nurses who interviewed them at baseline. The second posttest will allow us to determine whether the positive effect of the intervention on prediction accuracy, if any, is maintained for at least six months. Copies of completed *My Preferences *are made at the first posttest and, for those who have yet to complete one, at the second posttest. Allocating six months to fill out *My Preferences *gives participants extra time to decide whether they want to commit directives in writing. A longer interval carries the risk of losing too many participants and no longer permits attributing the observed effect to the intervention, as opposed to more recent events that might have occurred in the meantime. Evidence regarding the impact of the intervention on the rate of completed guides will be based on written documents rather than self-report as the latter was found to overestimate true completion rates [39].

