### Cost Analysis

To measure the intervention's financial impact, we will use the goals of care chosen by the older adults and their proxies at baseline and at the second posttest for the various health events. These goals of care will have been transformed into costs previously. The differential cost between the decisions made at baseline by the older adults in the experimental group and those made by their proxies for all scenarios will be deducted from the differential cost at posttest 2. To establish the net effect, the results will be compared with those of the control group calculated with the same method.

Three steps are required to cost each of the possible healthcare scenarios (health states × goals of care × health events): 1) identifying the healthcare resources required; 2) measuring the amount of resources previously identified; and 3) costing each resource [67,68].

As in previous studies [53,69,70], to identify the resources to be costed, we considered the health care and services that could be influenced by the preferences of the older adults or their proxies and could thus generate different costs. Therefore, we will value the healthcare services delivered essentially by the public healthcare system: hospital stays, nursing and assisted care, general and specialized medical care, ambulance transportation and other direct or indirect treatment-related costs. We will disregard healthcare services provided by family members on a volunteer basis.

To determine the number of resources required, we asked three physicians to create a treatment profile for each scenario, which were later validated from existing care protocols [71-78]. Relying on their expertise and experience, the physicians established a list of healthcare services based on the most frequent situations in their practice for cases similar to the various scenarios provided. These treatment profiles therefore combine a number of healthcare services to make up a "typical" treatment for each scenario in the study.

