### Potential limitations

People who agree to participate may differ to some extent from those who refuse. In particular, participants may be more favorable towards ADs - especially research ADs - than non-participants. Information gathered during the first telephone contact with prospective subjects will provide some data to compare participants with those who decline participation.

Participants are not explicitly informed of the study hypotheses. However, they cannot be blinded completely to group assignment. This design feature may exert some influence on their decision to complete *My Preferences*. However, it is unlikely to affect the primary outcome (prediction accuracy of substitute decisions) since dyad members are tested in separate rooms with vignettes that differ in part from those used at baseline. The use of control dyads partially controls for the Hawthorne effect on outcome measures. Furthermore, to ensure that participants who choose to express their preferences in writing understand the purposes and uses of written ADs, all participants are administered a brief knowledge questionnaire at the last posttest.

Every effort is made to keep research nurses blind to group assignment, including instructing participants not to reveal their group assignment. Unblinding may occur in some cases but this should not affect results since concordance is assessed by two nurses in separate rooms. While nurses may inadvertently discover that the dyad was exposed to the intervention (or not), this knowledge cannot impact concordance as they are unaware of the answers given by the other dyad member. Contamination is highly unlikely since controls do not meet their experimental counterparts and the consent form does not detail the tested intervention. Co-interventions are also unlikely given the relatively short duration of the intervention and scarcity of AD promotional efforts in the province of Quebec.

Last but not least, hypothetical vignettes do not generate the emotional reactions that characterize real-life situations. In addition, preferences may change as a result of declining health. Despite these drawbacks, the use of hypothetical scenarios in eliciting preferences for times of incapacity is common practice in advance care planning and research on substitute decision-making. More importantly, the intervention raises participants' awareness of the importance of updating ADs regularly.

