### Statistical analyses

Persons who decline participation or drop out will be compared to trial participants with parametric or non-parametric two-sample tests (depending on the distribution of the data) and results used to judge the scope of study findings. The same tests will be used to compare participants' baseline characteristics across study groups. Potential confounders and compliance indices will be candidates for adjustment when testing the impact of the intervention on the outcome measures [82]. All analyses will be based on allocation to the intervention or control group (i.e. by intention-to-treat). To account for losses to follow-up, analyses will be conducted in duplicate, first restricting the sample to the dyads for which we have complete follow-up data, then using a conservative approach by which dyads that do not provide such data are assumed not to have documented preferences and their baseline concordance levels are used for imputation [83].

The primary analysis will involve calculating composite scores of agreement across health states for each dyad. Calculations will generate a total concordance score as well as sub-scores derived from restricting summations to the clinical or research vignettes. Growth-curve modeling implemented with SAS PROC MIXED will be used to compare composite scores across time points and groups, an approach that accounts for the within-dyad correlation over time and accommodates missing values [84,85]. To further elucidate the impact of the intervention, secondary analyses will involve applying the same statistical procedure to the concordance sub-scores. A multivariable logistic model will be used to compare group-specific completion rates of *My Preferences *6 months post-intervention. The financial impact of the intervention will be investigated with Student's *t *test for independent samples or its non-parametric equivalent.

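### On its plain reading, the six-month posttest reuses the baseline vignettes whose results only the experimental arm discussed, so retained feedback may favour the intervention there and in the cost effect

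*Protocol article*

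**What the plan says.** Under Primary and secondary outcome measures, concordance is reassessed at the end of the intervention and "6 months later (second posttest), according to the same procedure as at baseline". One departure follows: "However, the first posttest uses new sets of treatments, sudden health events and research protocols to counter recall bias". The same section gives the second posttest the job of showing whether any gain in accuracy lasts six months.

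Under Baseline concordance assessment: "Results are compiled as soon as the interviews are completed, and communicated to experimental dyads at the start of the intervention". Under Intervention in the experimental group, at the first home visit "the facilitator summarizes the dyad-specific results of the concordance assessment and invites dyad members to discuss the reasons underlying their choices". The control section describes no counterpart; there, "dyads assigned to the control group are invited to attend a 2-hour health education workshop on healthy lifestyle and preventive practices".

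Under Cost Analysis, "we will use the goals of care chosen by the older adults and their proxies at baseline and at the second posttest", with the baseline cost differential deducted from the later one and the result compared with controls. Under Statistical analyses, "Growth-curve modeling implemented with SAS PROC MIXED will be used to compare composite scores across time points and groups". Under Potential limitations, incomplete blinding of participants is thought unlikely to affect the primary outcome because "dyad members are tested in separate rooms with vignettes that differ in part from those used at baseline".

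**The concern.** The protocol treats recall as a threat and changes the items at the first posttest for that reason. It states no such protection for the second. If the baseline items return, they are the items on which experimental dyads, and only they, have heard and discussed how proxy and older adult answered. An experimental proxy can then score higher by remembering a particular answer, with no gain in the ability to predict in situations that were not discussed. An older adult may likewise repeat the answer that was talked through.

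This is not ordinary retest memory, which would be similar in both arms and would largely cancel. It comes from feedback given to one arm. At stake are the claim that the effect lasts six months, the second posttest's contribution to the primary growth-curve analysis, and the cost effect, whose only follow-up time point is that visit.

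**Working it through.** **1. Which items are used at each visit, and who has had feedback on them**

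| Visit | Item sets | Feedback, experimental arm | Feedback, control arm |
|---|---|---|---|
| Baseline | Baseline sets | None yet | None |
| Posttest 1 | New sets (stated) | None described on these sets | None described |
| Posttest 2 | Baseline sets (inferred) | Results summarised and discussed | None described |

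The last row is an inference. Both posttests follow the baseline procedure, and the exception names the first only. The cost contrast from baseline to posttest 2 skips the visit with different health events, which fits. No sentence states the reuse outright.

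**2. Interval.** Feedback is given at the first of three monthly meetings. The end of the intervention is about 2 to 3 months later, and posttest 2 follows 6 months after that: 2 + 6 = 8 to 3 + 6 = 9 months between feedback and posttest 2.

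**3. What rests on posttest 2**
- The six-month conclusion: entirely.
- The cost effect: its only follow-up measurement.
- The growth-curve model: in part, since it uses all three time points.
- The posttest 1 comparison: not at all.

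**4. The limitations argument.** Separate rooms stop cross-talk during testing, not memory of answers disclosed months before. The only change of vignettes stated anywhere is at posttest 1, so the second half of the argument covers posttest 1 alone.

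**5. The plan's own sample size.** Inputs from Sample size: standardized difference d = 0.43, two-sided α = 0.05, 80% power, t statistic. With df = 2n − 2 and noncentrality d·√(n/2), power is 0.796 at n = 85 and 0.8006 at n = 86, so 86 per group is reproduced. Attrition: 120 × 0.9 = 108 and 108 × 0.8 = 86.4, matching the stated 108 and 86. None of this depends on which vignettes are used.

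**6. Illustration of scale (assumptions, not estimates).** Let a be accuracy without intervention, SD the between-dyad standard deviation of the concordance score as a proportion, and r the share of otherwise discordant items that experimental proxies get right by recall alone. Then

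recall-only standardized difference = r × (1 − a) / SD.

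Take a = 0.68, the pooled accuracy in Results from recent systematic reviews. It comes from treatment decisions and is applied here to the whole score. The SD is not given in the article; 0.10 to 0.20 is assumed.

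| r | SD 0.10 | SD 0.20 |
|---|---|---|
| 10% | 0.10 × 0.32 / 0.10 = 0.32 | 0.10 × 0.32 / 0.20 = 0.16 |
| 20% | 0.20 × 0.32 / 0.10 = 0.64 | 0.20 × 0.32 / 0.20 = 0.32 |

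The r at which recall alone equals the planned 0.43 is 0.43 × SD / 0.32: about 13% (SD 0.10), 20% (SD 0.15) or 27% (SD 0.20). With the same review's accuracy for scenarios of current health (79%), these become 0.43 × SD / 0.21 = 20%, 31% and 41%; with its figure for dementia scenarios (58%), 0.43 × SD / 0.42 = 10%, 15% and 20%.

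**The case against.** The strongest reply is that conveying wishes is the intervention. A proxy who still remembers, eight months on, what the relative wants in a given state does know that wish, and that is a benefit. This stands. It narrows the point to what posttest 2 cannot do: separate retained knowledge of discussed items from prediction in new scenarios, a distinction the protocol itself draws at posttest 1.

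Other replies also carry weight. Reuse of the baseline sets is inferred, and a condensed article may leave form content to the full protocol. The facilitator summarises results; nothing says every discordant item is shown. Eight to nine months weakens memory. The article accepts that preferences may change, so a remembered baseline answer may even be wrong. All of this lowers the likely size of the bias. None of it makes exposure equal between arms.

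A reader might infer more than the documents support:
- **That the six-month effect is merely recall.** Nothing in the article fixes a recall rate, and the illustration assumes one.
- **That maintenance cannot be judged at all.** Both arms receive the same set at each visit, so differences in item difficulty largely cancel between groups. What remains is the one-sided feedback.
- **That the primary analysis or the 86 per group fails.** Posttest 1 is protected, the model uses all visits, and the sample size is correct.
- **That the limitations section contradicts the outcome section.** Vignettes differing in part is literally compatible with new sets at posttest 1 only. The argument is incomplete, not false.

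**Conclusion.** The concern holds as a one-sided risk of bias at posttest 2. It rests on the plain reading that this visit returns to the baseline sets, and on feedback being given to experimental dyads only. On that basis the group difference at posttest 2 mixes retained feedback with general predictive ability, and the likely direction favours the intervention. The six-month conclusion and the cost effect are exposed directly, the growth-curve result only through its last time point. The posttest 1 result stands.

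The size cannot be derived from the article. The illustration shows only that modest recall could matter beside a planned difference of 0.43; it assumes the SD, the recall share and stable preferences. If posttest 2 is collected on the discussed items alone, its data cannot separate the two components afterwards, so the item sets should be settled before that visit takes place.

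**What to change.** 1. In Primary and secondary outcome measures, state which sets each posttest uses, and specify that the primary concordance score at posttest 2 is based on the posttest 1 sets, for which no feedback is described.
2. Ask the baseline health events at the end of the posttest 2 interview, for the stated cost analysis only and outside the primary score. State in Cost Analysis that the cost effect includes recall of items discussed during the intervention. Costing the posttest 1 events instead is not an option under the stated method, because those events have no baseline measurement to deduct.
3. In Potential limitations, say at which visits the vignettes differ from baseline, and that separate rooms do not prevent recall of earlier feedback.

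Cost: a slightly longer posttest 2 interview, with no new vignettes, dyads or visits. The posttest 1 items would be repeated after six months, an interval that is the same in both arms. The primary score would have no same-item comparison with baseline at posttest 2, as is already the case at posttest 1.

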### Cost Analysis

To measure the intervention's financial impact, we will use the goals of care chosen by the older adults and their proxies at baseline and at the second posttest for the various health events. These goals of care will have been transformed into costs previously. The differential cost between the decisions made at baseline by the older adults in the experimental group and those made by their proxies for all scenarios will be deducted from the differential cost at posttest 2. To establish the net effect, the results will be compared with those of the control group calculated with the same method.

Three steps are required to cost each of the possible healthcare scenarios (health states × goals of care × health events): 1) identifying the healthcare resources required; 2) measuring the amount of resources previously identified; and 3) costing each resource [67,68].

As in previous studies [53,69,70], to identify the resources to be costed, we considered the health care and services that could be influenced by the preferences of the older adults or their proxies and could thus generate different costs. Therefore, we will value the healthcare services delivered essentially by the public healthcare system: hospital stays, nursing and assisted care, general and specialized medical care, ambulance transportation and other direct or indirect treatment-related costs. We will disregard healthcare services provided by family members on a volunteer basis.

To determine the number of resources required, we asked three physicians to create a treatment profile for each scenario, which were later validated from existing care protocols [71-78]. Relying on their expertise and experience, the physicians established a list of healthcare services based on the most frequent situations in their practice for cases similar to the various scenarios provided. These treatment profiles therefore combine a number of healthcare services to make up a "typical" treatment for each scenario in the study.

Costing each identified resource is the last step. Although the cost of the resources should normally be their opportunity cost [67,79], we will in fact be using the market cost, which is considered to be equivalent [79,80]. Therefore, the value of medical and nursing care will be based on the salary earned by a physician or health professional [67,81] while materials required for treatments will be valued at their purchase price. When it will not be deemed pertinent to determine the value of a resource according to the amount spent, because that amount is no longer representative of its value (as with infrastructures, for example), we will use the market value [67,81]. Various data (government statistics, financial reports from healthcare institutions, etc.) will be used to establish resource costs, which will be set in 2010 dollars. Where appropriate, a government indexation rate will be applied [67].

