**Discussion:**

This study will determine whether the tested intervention guides proxies in making decisions that concur with those of older adults, motivates the latter to record their wishes in writing, and yields savings for the healthcare system.

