### The research objectives

The purpose of this trial is to assess the efficacy of a multimodal professionally-led advance planning intervention in 1) improving the accuracy of substitute decision-making (primary outcome) and 2) increasing the frequency of written ADs for health care and research (secondary outcome). Given current knowledge, the tested intervention includes an educational component on ADs and stimulates discussion between an older adult and his/her self-selected proxy with respect to end-of-life care and research participation. The study incorporates a cost analysis to measure public savings that result from improving proxy predictions of preferences.

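### The change in the older adult–proxy cost differential, with delivery cost left out, cannot by itself establish savings for the healthcare system

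*Protocol article*

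**What the plan says.** The protocol states its cost aim in two ways. The research objectives are narrow: "The study incorporates a cost analysis to measure public savings that result from improving proxy predictions of preferences". The Discussion paragraph of the Abstract is broader and says the trial will determine whether the intervention "yields savings for the healthcare system". The main Discussion repeats the cost-savings aim and looks ahead to routine use, with physicians referring patients to a social worker who would deliver the intervention.

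The Cost Analysis section converts the goals of care chosen by each dyad member into costs. It starts from the gap between the two members at baseline: "The differential cost between the decisions made at baseline by the older adults in the experimental group and those made by their proxies". This gap, taken over all scenarios, "will be deducted from the differential cost at posttest 2". It then adds: "To establish the net effect, the results will be compared with those of the control group calculated with the same method". It does not say whether the gap is older adult minus proxy, proxy minus older adult, or an absolute value.

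On which resources to price, the section says "we considered the health care and services that could be influenced by the preferences of the older adults or their proxies". The list that follows covers hospital, nursing, medical, ambulance and other treatment-linked costs. It contains no item for delivering the intervention.

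**The concern.** Two features separate this outcome from public spending.

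- **The differential has two moving parts.** Once an older adult is incapacitated, the care that is paid for follows the proxy's decision. The section on the Quebec legal landscape says relatives may decide, taking known wishes into account. The differential, however, also moves when the older adult's own answers move. The experimental intervention works on those answers: older adults see their concordance results, discuss their reasons and are helped to articulate preferences. Controls attend healthy-lifestyle workshops.
- **The pricing rule leaves out an input.** Home visits by social workers, the group session and the printed guide are not care that depends on the preference chosen, so they fall outside the rule.

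At stake is a policy-facing statement that the intervention does or does not save money. It could have the wrong size or, under the absolute reading, the wrong direction.

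**Working it through.** The plan gives no cost figure to reproduce, so the check is on the formula. All cost units below are assumed for illustration.

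**Definitions.** E is the cost of the older adult's choices and P the cost of the proxy's choices; 0 is baseline and 2 is posttest 2. Taking the gap as E − P (an assumption):

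M = [(E2 − P2) − (E0 − P0)] experimental − [same] control

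Rearranged: M = (between-arm difference in change of E) − (between-arm difference in change of P). Only the second term concerns the care that proxies choose.

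**Cases.** Control dyads are unchanged throughout: E = 10, P = 15 in A to C; E = 15, P = 10 in D.

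| Case (experimental arm) | E0→E2 | P0→P2 | M as E−P | M as P−E | M as absolute gap | Change in proxy-chosen cost |
|---|---|---|---|---|---|---|
| A: proxy aligns down | 10→10 | 15→10 | +5 | −5 | −5 | −5 |
| B: older adult moves up | 10→15 | 15→15 | +5 | −5 | −5 | 0 |
| C: both fall | 10→5 | 15→10 | 0 | 0 | 0 | −5 |
| D: under-treating proxy aligns up | 15→15 | 10→15 | −5 | +5 | −5 | +5 |

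For example, A is (10 − 10) − (10 − 15) = +5 and B is (15 − 15) − (10 − 15) = +5. A and B are indistinguishable on every reading, though only A saves anything. C saves 5 and scores 0 on every reading. In D the absolute gap gives the same −5 as in A, although proxy-chosen cost rises by 5.

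**What the control arm removes.** Let E rise from 10 to 15 in both arms, with P going 15→10 in the experimental arm and staying at 15 in control. Experimental: (15 − 10) − (10 − 15) = +10. Control: (15 − 15) − (10 − 15) = +5. M = +5, which matches the true fall of 5. Drift common to both arms therefore cancels under a signed reading. Under the absolute reading it need not: (5 − 5) − (0 − 5) = +5, which looks like a widening gap.

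**Delivery input.** The Trial interventions section gives three 2-hour meetings per experimental dyad. Two are home visits led by social workers (2 × 2 = 4 hours per dyad), and one is a 2-hour group session shared by several dyads. Controls also have three 2-hour meetings, all in groups. No wage, travel or material cost is given, so no net figure can be computed.

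**The case against.** The strongest defence is that the stated objective concerns savings from better proxy prediction, and the gap between older adult and proxy is a natural measure of that. On this view the zero in case C is right: both moved together and prediction did not improve. This stands as a reason to keep the differential. It does not meet case B, where the gap closes because the older adult moved and nothing is saved. Nor does it cover the broader promise about the healthcare system.

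Second, the control comparison removes shared drift, and the protocol attributes preference change to life events and declining health, which affect both arms. That also stands, for a signed gap. The problem needs a shift caused by the intervention, which is plausible from its content but not something the protocol states will happen.

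Third, the resource rule appears under the costing of scenarios, and a journal article is condensed. But it is an affirmative rule that delivery items do not meet, not mere silence, and no other part of the article says delivery will be costed.

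Three stronger inferences are not supported:

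- A reader might take the phrase net effect as a claim to be net of programme cost. In context it means net of control.
- A reader might multiply four health states by three health events and infer that savings are overstated up to twelvefold. The article says all scenarios are used but gives no weights or aggregation rule, which is ordinary analysis-plan detail.
- A reader might put a dollar figure on the omitted delivery cost. The article gives no rates, and the control arm's meetings make any between-arm increment smaller than the gross cost.

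**Conclusion.** The point holds in a limited form. The planned differential does not by itself establish savings for the healthcare system: a change in it is neither necessary nor sufficient for a change in the cost of the care proxies choose. This rests on two assumptions: spending under incapacity follows the proxy's decision, and the intervention shifts older adults' choices differently from control. If older adults' choices shift equally in both arms, a signed differential does equal the gross change in proxy-chosen cost (with the sign reversed when taken as E − P), so a reader should not infer that the measure can never reflect savings. Separately, without delivery cost the result is at most a gross change in care cost.

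The size of the error in money cannot be derived from the document. Cost is neither the primary nor the secondary outcome, and the sample size is unaffected. This is an inexpensive improvement worth making because it changes what may be concluded.

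**What to change.** 1. State whether the differential is signed, and in which direction.
2. Report older adult costs and proxy costs separately by arm, at baseline and posttest 2.
3. Base any savings conclusion on the between-arm comparison of proxy-chosen cost at posttest 2, adjusted for baseline proxy cost. This replaces the two-sample test in Statistical analyses for that conclusion.
4. Keep the differential as the measure of cost discrepancy due to inaccurate prediction, which is what the research objectives describe.
5. Add the delivery cost per dyad in each arm from trial records (staff time, home visits, group sessions, printed guide) and report the net figure. Otherwise, restrict the conclusion to gross care-cost differences in hypothetical decisions.

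No new participant data are needed, since the proxies' goals of care are already collected and costed at both times. The price is some extra costing of inputs the trial already pays for, and savings may look smaller.
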